#### 2.3.3. Anesthesia and Analgesia

Standard care will be provided for patients in two groups after arriving in the operating room, which includes pulse oximetry saturation (SpO_2_), heart rate (HR), non-invasive blood pressure (BP), and end-tidal carbon dioxide partial pressure (P_ET_CO_2_). Anesthesia will be induced with 8 mg of dexamethasone, sufentanil 0.3–0.5 μg kg^−1^, propofol 2–3 mg kg^−1^, and rocuroium 0.6 mg kg^−1^ when peripheral vascular access is obtained. After that, P_ET_CO_2_ will be maintained at 35–45 mmHg by a volume-controlled mechanical ventilation mode with a tidal volume 6–8 mL kg^−1^, and the respiratory rate 12–15 breaths per minute. Maintenance of anesthesia through continuous infusion of remifentanil (0.1–0.2 μg kg^−1^ min^−1^) and propofol (6–8 mg kg^−1^ h^−1^) will be conducted to maintain stable hemodynamics after anesthesia induction. In total, 10 µg of sufentanil will be provided 30 min before the end of surgery, and propofol and remifentanil infusion will be discontinued after surgery.

Corresponding treatment will be administered if mean arterial pressure exceeds 20% of the baseline value. The total dosage of analgesics and anesthetics will be assessed following surgery. After surgery, the anesthesiology will transfer patients to the PACU without providing patient-controlled analgesia. In total, 40 mg of parecoxib sodium will be administered as rescue treatment for patients whose NRS score is higher than 4 in the PACU or ward. If patients experience nausea or vomiting in the PACU or on discharge to the ward, they will be administered 4 mg of ondansetron.

#### 2.3.4. Adverse Event

All AEs will be recorded through the symptoms reported by the patients at each visit. Nerve-block-related AEs might include hematoma and infection in the block site, and pneumothorax and local anesthetic toxicity. If a patient is suspected to be affected by local anesthetic poisoning, an immediate stop to the nerve blocks and an active rescue treatment will be administered.

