#### 2.1.3. Outcome Measures

The QoR-15 questionnaire will be used to measure the patients’ quality of recovery at 24 h, 72 h, and 1 month after operation. A higher QoR-15 score (from 0 to 150) suggests greater recovery after surgery. The NRS score will be used to measure postoperative pain, and a higher score indicates more severe pain after surgery. The NRS scores will be recorded before discharge from PACU at 24 h, 72 h, and 1 month following surgery. Neuropathic pain will be assessed before surgery by a modified Douleur Neuropathique 4 (DN4) questionnaire on a scale of 0–10. A total DN4 score of more than or equal to 4 indicates neuropathic pain.

Emergence agitation is identified as improper behavior that presents itself as excitation, agitation, and concurrent orientation disorder during the anesthesia recovery phase. Respiratory recovery time refers to the interval between the end of anesthetic drugs and respiratory recovery. Response time is defined as the interval between the cessation of anesthetic drugs and response to a verbal command. Duration of time between the cessation of anesthetic drugs and extubation is referred to as the extubation time.

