### 2.3. Interventional Methods

#### 2.3.1. Intervention

Participants randomized to the SNB group will receive general anesthesia combined with SNB and ICNB using 0.5% ropivacaine, which will be performed exclusively by an attending anesthesiologist. Meanwhile, patients in the control group will receive general anesthesia without the nerve blocks. An attending anesthesiologist will select the sites of the nerve blocks based on the surgical incision site. After negative aspiration, the scalp nerve will be blocked, including the greater occipital nerve (2–3 mL), superficial temporal nerve (2–3 mL), trochlear nerve (2–3 mL), and supraorbital nerve (2–3 mL). The total volume in SNB will not exceed 10 mL.

Ultrasound-guided unilateral ICNB will be conducted at the plane of T4–T5 next to the sternum in patients who are in the supine position. A longitudinally oriented, linear ultrasonic probe will be used to determine the pleura, internal intercostal muscles, rib, and innermost intercostal muscles. An echogenic needle will be inserted using an in-plane technique to target the inferior margin of rib. A volume of 10–15 mL with 0.5% ropivacaine will be injected into the intercostal spaces where the incision locates after negative aspiration. ICNB is considered successful when pleural movement is observed in intercostal spaces.

The block efficacy for formal dermatomal sensory will not be formally tested because patients under general anesthesia are unconscious. The anesthesiologist performing the nerve blocks will not visit patients in the perioperative period. After the nerve blocks, the anesthesiologist will cover the dressing at the relevant areas to hide the allocation. Only the dressing will be covered in the same site of the control group without injecting normal saline, in consideration of ethical care.

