### 2.4. Randomization and Blinding

Patients will be randomly assigned to the SNB group and control group in a ratio of 1:1 using random number tables generated by a computer, including numbers 1–88 which is performed by an anesthesia nurse. The patients corresponding to the first 44 random numbers will be assigned to the control group, while the rest will be allocated to the SNB group. An anesthesia nurse with no direct clinical role in the trial will type the group assignment on separate papers, fold them up, and put them inside sequentially numbered sealed opaque envelopes.

Attending anesthesiologists who are not involved in the follow-up will perform SNB combined with ICNB after the induction of general anesthesia. Participants will be informed as to whether they will receive nerve blocks or not by the research coordinator, who will not participate in treatment or evaluation. Therefore, the attending anesthesiologists, research coordinator, and anesthesia nurse will know the allocation schedule. Group assignment will be concealed from patients, anesthesiologists responsible for operation, and investigators who are in charge of assessing and collecting data. Group allocation will not be disclosed until all data collection is completed. After consultation with the principal investigator (PI), the blinding will be removed if a concern regarding local anesthetic toxicity arises.

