## Figures and Tables

**Figure 1 brainsci-12-01007-f001:**
[figure not shown]
Flow chart of participants in the trial.

**Table 1 brainsci-12-01007-t001:** The schedule of enrollment, interventions, and assessments for the trial.

		Enrollment	Allocation	Postallocation					Postoperative		
Time point				Induction	Postinduction	Operation	PACU	PACU discharge	24 h	72 h	1 m
Enrollment		**×**									
Eligibility screen		**×**									
Informed consent		**×**									
Allocation			**×**								
Basic information		**×**									
Interventions											
SNB group	Blocking				**×**						
	Dressing				**×**						
Control group	Blocking										
	Dressing				**×**						
Assessment											
QoR-15 scores									**×**	**×**	**×**
NRS scores								**×**	**×**	**×**	**×**
PONV											
Remifentanil consumption											
Rescue analgesics											
Emergence agitation							**×**				
Anesthesia duration											
Operation duration						**×**					
Respiratory recovery time							**×**				
Response time							**×**				
Extubation time							**×**				
PACU LOS							**×**				
DN4		**×**									
AEs					**×**	**×**	**×**	**×**	**×**	**×**	**×**

SNB, scalp nerve block; QoR, quality of recovery; NRS, numeric rating scale; PONV, postoperative nausea and vomiting; PACU, postanesthesia care unit; LOS, length of stay; DN4, Douleur Neuropathique 4; AEs, adverse events.

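### The rule that every adverse event comes from patient-reported symptoms cannot work at the postinduction and operation assessments in Table 1, so some intraoperative block harms may be absent from the adverse event outcome

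*Protocol article*

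**What the plan says.** Section 2.3.4 (Adverse Event) sets the recording rule: "All AEs will be recorded through the symptoms reported by the patients at each visit". It then lists the harms to be expected: "Nerve-block-related AEs might include hematoma and infection in the block site, and pneumothorax and local anesthetic toxicity".

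On timing, section 2.4 states that the attending anesthesiologists "will perform SNB combined with ICNB after the induction of general anesthesia", and Table 1 places blocking in the postinduction column. Section 2.3.1 explains the lack of a formal sensory test of the block by noting that "patients under general anesthesia are unconscious".

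Table 1 ("The schedule of enrollment, interventions, and assessments for the trial") marks adverse events at postinduction, operation, PACU, PACU discharge, 24 h, 72 h and 1 month.

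Block-related adverse events are a secondary outcome (sections 1 and 2.1.2). Pneumothorax and local anesthetic toxicity are among the situations for termination in section 2.3.2.

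**The concern.** The protocol accepts that an anesthetized patient cannot take part in a sensory test, yet for the same period it relies on that patient's report of symptoms for safety. Toxicity, or a pneumothorax at the moment of injection, would show first as signs seen by staff or on the monitor. A rule confined to reported symptoms does not cover an event that was seen and treated, and had resolved before the patient woke.

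What is at stake is the credibility of the safety result. Only the SNB group is exposed to the blocks, so any loss of block-related events falls on that group and makes the intervention look safer than it is.

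**Working it through.** The protocol states no figure on this point, so there is none to reproduce. The check sets the sections side by side.

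**1. Can the stated method work at each scheduled time point?**

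| Adverse event column in Table 1 | Patient's state | Can symptoms be reported? |
|---|---|---|
| Postinduction (blocks given here) | under general anesthesia | no |
| Operation | under general anesthesia | no |
| PACU | emerging | only in part |
| PACU discharge | awake | yes |
| 24 h, 72 h, 1 month | awake | yes |

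The PACU entry follows from section 2.1.3: "Response time is defined as the interval between the cessation of anesthetic drugs and response to a verbal command". Table 1 times response, respiratory recovery and extubation in the PACU, so part of that period precedes responsiveness. Of seven columns, the method fails in two, works in part in one, and works in four (2 + 1 + 4 = 7).

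**2. Does another section supply a second source for adverse events?**

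- Section 2.3.3 describes monitoring ("Standard care will be provided for patients in two groups after arriving in the operating room": SpO2, heart rate, blood pressure, end-tidal CO2). It does not link this to adverse event recording.
- Section 2.5.1 has the anesthesiologists in charge record intraoperative data, and a blinded investigator collect the other secondary outcome data. Adverse events are not named in either role.
- Sections 2.3.4 and 2.4 provide for action and unblinding when toxicity is suspected. These presuppose that a clinician recognizes it, but they govern management and not what is entered as an adverse event.
- Sections 2.3.1 and 2.4 keep the anesthesiologist who gives the block out of follow-up, so the best-placed witness is not present when symptoms are collected.

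**3. Which of the four named harms are exposed?**

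- Local anesthetic toxicity: exposed if it begins and resolves under anesthesia.
- Pneumothorax: exposed if it causes no symptoms; if it persists, it may be reported later.
- Hematoma and infection at the block site: may be reported at later visits.

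**4. What would incomplete capture do? (Illustration with assumed values.)**

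Input: 44 block patients (section 2.4). With no recorded event and complete capture, the exact one-sided 95% upper bound for the true rate is 1 − 0.05^(1/44) = 6.6%. If only a share c of events is recorded, the bound becomes 6.6%/c: 13.2% for c = 0.5 and 26.3% for c = 0.25. At an assumed true rate of 2%, the chance of recording at least one event is 1 − (1 − 0.02c)^44: 59% for c = 1, 36% for c = 0.5 and 20% for c = 0.25. The values of c and the 2% are assumptions; the documents give neither. The figures show how sensitive a report of no events is to capture. They do not estimate how much this rule loses.

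**The case against.** The strongest reply is that the sentence speaks of visits, and the induction room and operating theatre are not ordinarily called visits. On that reading it governs follow-up in the ward and clinic, while section 2.5.1 covers the operating room. Table 1 already plans assessment at the early points. A recognized toxicity reaction would bring rescue treatment, consultation with the principal investigator and possible unblinding, and the DSMB reviews safety monthly with access to unblinded data. Checklists and definitions belong to the full protocol and the CRF.

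Much of this stands. A reader might infer that intraoperative harms have no route at all into the data, or that the main block harms in general would be missed. The documents support neither: intraoperative data are recorded, clinician recognition is presumed in several sections, and some of the named harms can surface later. Nor does the 6.6% bound measure the defect; it holds for any trial with 44 exposed patients and no events.

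The narrower reading does not remove the conflict, however. The sentence covers all adverse events, Table 1 places adverse event assessment where that method cannot operate, and no section assigns the intraoperative record to that purpose. The absence of a CRF checklist is no finding; a stated rule that cannot be carried out at scheduled time points is one.

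**Conclusion.** The point holds as a conflict between the recording rule in section 2.3.4 and the schedule in Table 1, affecting two of seven time points fully and one in part. The likely loss is confined to transient intraoperative events and a pneumothorax without symptoms, and concerns what enters the adverse event outcome, not whether staff would notice or treat the event. Its size cannot be determined from the documents. The conclusion assumes that the rule is applied as written; if staff in practice transfer events from the anesthesia record, the loss shrinks or disappears. The primary outcome and the randomization are untouched. The correction should be made because the outcome is a listed one and the change is cheap.

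**What to change.** Reconcile section 2.3.4 with Table 1 and section 2.5.1. State that adverse events at postinduction, operation and PACU are recorded in both arms from clinician-observed signs in the existing anesthesia and PACU records, and that patient-reported symptoms are added from PACU discharge onward. Apply the same source and procedure to both groups.

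Do not add inspection under the dressings by blinded staff: the dressings conceal allocation, and looking beneath them could reveal who was injected. No clinical management rule needs to change.

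The cost is about one sentence, a little more abstraction from records already kept, and possibly a higher count of recorded adverse events.

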### 2.4. Randomization and Blinding

Patients will be randomly assigned to the SNB group and control group in a ratio of 1:1 using random number tables generated by a computer, including numbers 1–88 which is performed by an anesthesia nurse. The patients corresponding to the first 44 random numbers will be assigned to the control group, while the rest will be allocated to the SNB group. An anesthesia nurse with no direct clinical role in the trial will type the group assignment on separate papers, fold them up, and put them inside sequentially numbered sealed opaque envelopes.

Attending anesthesiologists who are not involved in the follow-up will perform SNB combined with ICNB after the induction of general anesthesia. Participants will be informed as to whether they will receive nerve blocks or not by the research coordinator, who will not participate in treatment or evaluation. Therefore, the attending anesthesiologists, research coordinator, and anesthesia nurse will know the allocation schedule. Group assignment will be concealed from patients, anesthesiologists responsible for operation, and investigators who are in charge of assessing and collecting data. Group allocation will not be disclosed until all data collection is completed. After consultation with the principal investigator (PI), the blinding will be removed if a concern regarding local anesthetic toxicity arises.

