#### 2.1.4. Sample Size and Recruitment

The study’s primary outcome is the scores of QoR-15 at 24 h after surgery. Our preliminary study showed that the scores of QoR-15 at 24 h following DBS operation in PD patients without nerve block were equivalent to 110 (10.1). A previous study has shown that the QoR-15 score change of 8 points was deemed to be a clinically significant difference [26]. We calculated the required number of patients using PASS 11 software (NCSS, Kaysville, UT, USA) with an alpha error of 0.05 and power 95% (test for two proportions, two-sided *t*-test), and determined that 35 patients would need to be included in each group. Considering a 20% dropout rate, we defined a sample size of 88 participants.

Recruitment will be performed during a 12-month period. The study will end when the last patient enrolled undergoes an assessment of QoR 1 month after surgery. The protocol has been initiated as planned in April 2022 and will be completed in March 2023.

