### 2.2. Selection of Subjects

#### 2.2.1. Participants

Participants who will undergo elective DBS surgery will be informed of the trial before surgery. Interested participants can contact the research coordinator to acquire more information about the study purpose and protocol. The clinical research coordinator will interview potential subjects to assess whether they meet the inclusion and exclusion criteria. Written informed consent will be voluntarily provided by eligible participants to the research coordinator before randomization.

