#### 2.5.4. Statistical Analysis

Masked statistical analysts will conduct the analyses at the Clinical Research Center of Changhai Hospital. The full analysis set including all randomized patients and per protocol set, including patients with the primary outcome, will be performed. Safety and efficacy analyses will be conducted based on the intention-to-treat analysis population, which includes all randomized patients. Missing data will be handled using the mixed model for repeated measurements.

All statistical analysis will be performed by SPSS 23.0 statistical analysis software (IBM SPSS, Armonk, NY, USA). Continuous variables in normally distributed data represented as mean (SD) will be compared using the Student’s t-test, while continuous variables in non-normal distribution data reported as medians (quartiles) will be compared using Mann-Whitney *u* test. Categorical variables described as frequency and percentages will be compared using χ^2^ test or Fisher’s exact test. *p* < 0.05 will be regarded as statistically significant.

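### Allocation is scheduled before induction although the arms differ only in blocks done after it, so patients lost in between are randomised with no QoR-15 score

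*Protocol article*

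**What the plan says.** Four parts of the protocol article bear on this point.

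- **Consent and eligibility (2.2.1).** The research coordinator assesses eligibility at an interview, and "Written informed consent will be voluntarily provided by eligible participants to the research coordinator before randomization".
- **Order of events (Table 1, captioned "The schedule of enrollment, interventions, and assessments for the trial").** Allocation is a separate column after Enrollment. The next block is headed Postallocation, and its first column is Induction. Blocking (SNB group) and dressing (both groups) are marked only under Postinduction.
- **What differs between the arms (2.3.1, 2.4).** Section 2.4 says "Attending anesthesiologists who are not involved in the follow-up will perform SNB combined with ICNB after the induction of general anesthesia", while by 2.3.1 "patients in the control group will receive general anesthesia without the nerve blocks". Control patients get the dressing at the same site. Section 2.3.3 describes one anesthetic regimen for both groups.
- **Who is analysed, and how many (2.5.4, 2.4, 2.1.4).** The plan names "The full analysis set including all randomized patients" and runs efficacy and safety analyses by intention to treat. The list holds the numbers 1 to 88, 44 per arm. On losses the only allowance is this: "Considering a 20% dropout rate, we defined a sample size of 88 participants".

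Section 2.4 also says "Participants will be informed as to whether they will receive nerve blocks or not by the research coordinator", and then says that assignment is concealed from patients.

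**The concern.** Nothing in the assigned treatment differs between the arms until the patient is asleep, so the documents give no reason to allocate earlier. Doing so creates an interval in which a patient can be randomised and then never reach the point where treatment differs. Elective surgery can be cancelled and consent can be withdrawn. An exclusion such as infection at the block site can also come to light late: eligibility is judged at an interview, while the attending anesthesiologist chooses the block sites (2.3.1).

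Such a patient stays in an analysis of everyone randomised but contributes nothing to the primary outcome, and has used an allocation that an evaluable patient could have had. Whether bias is also at stake depends on the two conflicting statements in 2.4 about what patients know. If an awake patient has been told the arm, leaving before the block may be related to it.

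**Working it through.** **1. Is there a gap between allocation and the point where the arms diverge?** Table 1 gives the order Enrollment, Allocation, Induction, Postinduction (block and dressing). Section 2.4 independently places the block after induction. So there is a gap. Its length is not stated, nor is who opens the envelope or when.

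**2. What data would a patient lost in the gap have?** Table 1 marks QoR-15 at 24 h, 72 h and 1 month only, with no baseline. A patient who is not operated on therefore has no QoR-15 observation at any time. The mixed model for repeated measurements named in 2.5.4 has no outcome record for that patient to use.

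**3. The plan's own figures.** Inputs from 2.1.4: difference 8, SD 10.1, alpha 0.05, two-sided t-test, 95% power, 35 per group, 20% dropout, 88 in total.

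- The dropout step reproduces: 35 / (1 − 0.20) = 43.75, so 44 per arm and 88 in total.
- The 35 per group does not reproduce at two-sided 95% power. The noncentral t calculation needs 43; 35 corresponds to 90% power. That is a separate matter and the point here does not rest on it.

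**4. Power as patients are lost before the block.** With n evaluable per arm, the noncentrality is (8 / 10.1) × √(n / 2), on 2n − 2 degrees of freedom. Power is the probability that the absolute t statistic exceeds its two-sided 5% critical value.

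| Lost per arm | n per arm | Noncentrality | Critical t | Power |
|---|---|---|---|---|
| 0 | 44 | 3.715 | 1.988 | 95.7% |
| 2 | 42 | 3.630 | 1.989 | 94.8% |
| 4 | 40 | 3.542 | 1.991 | 93.8% |
| 9 | 35 | 3.314 | 1.995 | 90.4% |

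The last row assigns the whole 20% allowance to the interval before the block. It is an outer bound, not an estimate.

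**5. How this interacts with the 20% allowance.** Two readings are possible.

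- If the 20% covers every loss, 35 per arm remain as planned and early losses change nothing in the sample-size plan.
- If the 20% covers only losses after induction, early losses come on top. The documents give no rate, so 2%, 5% and 10% are assumptions. Evaluable patients per arm are 44 × (1 − f) × 0.80, rounded down: 34, 33 and 31. Power is 89.6%, 88.7% and 86.6%, against 90.4% at 35. Keeping 35 per arm would take 35 / (0.80 × (1 − f)) per arm, rounded up: 45, 47 and 49, or 90, 94 and 98 in total.

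**The case against.** The strongest reply is that the effect may be negligible. Table 1 gives an order and no times. Opening the envelope in the operating room minutes before induction would fit it, and losses in the gap would then be close to nil. Eligibility is screened before randomisation, and most of the terminations listed in 2.3.2 are postoperative and would not be prevented by later allocation. The 20% allowance may absorb the rest. All of this stands. It limits the size of the problem, but it does not justify the order that Table 1 fixes.

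A reader might infer more than the documents support in four ways.

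- **Induction doses, given as ranges in 2.3.3, chosen with knowledge of the arm.** Section 2.4 conceals assignment from the anesthesiologists responsible for the operation. The unmasked anesthesiologist is the one doing the block, who by 2.3.1 does not see patients perioperatively. As written, dosing cannot follow the arm.
- **Arm-related withdrawal as an established bias.** It is possible only if the sentence about informing participants is acted on. That sentence gives no time and contradicts the concealment stated in the same section.
- **Nine per arm as an expected loss.** No cancellation or late-ineligibility rate is given, so this is only the outer bound.
- **Later allocation as a cure for the analysis-set conflict.** Section 2.5.1 excludes patients who cannot complete the primary outcome, while 2.5.4 analyses all who were randomised. That conflict also covers postoperative dropouts and would remain.

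It is also fair to object that 2.1.4 reports the trial as started in April 2022. A change now is a mid-trial amendment, so it is cheap but not free.

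**Conclusion.** The point holds in a limited form. The schedule randomises patients before it needs to, and anyone lost between allocation and the block becomes a randomised patient without an outcome.

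The number affected cannot be derived from the documents. On the plan's difference and SD, two losses per arm cost about 1 percentage point of power (95.7% to 94.8%) and four cost about 2 (to 93.8%). If patients stay masked, the cost is this loss of precision and a less clean all-randomised set, not bias. If they are told their arm before the block, withdrawal related to the arm becomes possible as well. The conclusion rests on the column order in Table 1 and on there being no QoR-15 assessment before 24 h. Because a simple change removes these losses altogether, it is worth making even if they are few.

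**What to change.** 1. In 2.4, state that the anesthesiologist who performs the block opens the next sealed envelope after induction and a final eligibility check, immediately before the block. This person is already unmasked.
2. In Table 1, move Allocation to between Induction and Postinduction.
3. State that a consented patient who leaves before that point counts as not randomised, and that the unopened envelope passes to the next patient.
4. Delete the sentence in 2.4 saying that participants are told whether they will receive blocks. It contradicts concealment from patients and cannot coexist with allocation after induction.
5. Apply the change to patients not yet randomised and record its date, so that patients randomised under each rule can be identified.

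Cost: a small procedural amendment and a brief step in the operating room. The envelopes and staff are already in the plan, and no extra patients are needed. The conflict between 2.5.1 and 2.5.4 over patients without the primary outcome needs its own correction.

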The SNB—the blockage of nerves including the greater occipital nerve, superficial temporal nerve, trochlear nerve, and supraorbital nerve—was developed because of its potential advantages for powerful regional anesthesia administration. Moreover, it encourages the advancement of precise neurosurgery, functional, and micro-neurosurgery [22]. The ICNB was used to provide effective postoperative analgesia in chest surgery [21,23]. The incision of DBS surgery involves the distribution of scalp nerves and intercostal nerves; thus, SNB combined with ICNB may relieve postoperative pain in patients receiving DBS surgery.

The 15-item QoR (QoR-15) questionnaire is an outcome questionnaire reported by patients that assesses the quality of recovery following surgery and anesthesia [24]. The QoR-15 score includes five areas of health status reported by patients in order to provide a meaningful assessment of their total recovery experience: pain, physical comfort, physical independence, psychological state, and emotional state. It is a useful instrument in clinical studies or trials due to the measurement errors and reliability, and a higher QoR-15 score indicates better postoperative recovery.

The present study’s main objective is to evaluate the clinical efficacy of SNB combined with ICNB for the QoR after DBS surgery. Furthermore, the present study may provide a novel method for enhanced recovery and early prevention and treatment of acute pain after DBS surgery. We hypothesize that SNB combined with ICNB can improve the postoperative QoR of patients with PD. This is based on the clinical evidence that the involved region of the scalp and intercostal nerves can be blocked by SNB combined with ICNB, providing an extensive block and better analgesia.

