In this protocol, the attending anesthesiologist is not masked to the group assignment because they will be required to conduct the nerve block. However, researchers masked to the group allocation will evaluate the primary outcome. In addition, formal dermatomal evaluation of block efficacy will not be conducted because nerve blocks will be performed under general anesthesia. This increases the risk that certain blocks may not be completely effective. Scalp nerves are superficial and easy to block, and ICNB performed under ultrasound guidance is consistent with routine clinical practice. Thus, our results should still be generalizable to widespread clinical practice. Lastly, this study is a single-center study, which may result in bias. Nonetheless, the findings of the present study may promote the development of enhanced postoperative recovery and popularize the optimal pain management of patients with DBS surgery.

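### Section 2.4 says both that participants will be told whether they receive the blocks and that allocation is concealed from them, although the primary outcome is patient-reported

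*Protocol article*

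**What the plan says.** All the conflicting statements stand in one paragraph of section 2.4 (Randomization and Blinding).

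- Disclosure: "Participants will be informed as to whether they will receive nerve blocks or not by the research coordinator". The coordinator is described as taking no part in treatment or evaluation.
- Who holds the allocation: "Therefore, the attending anesthesiologists, research coordinator, and anesthesia nurse will know the allocation schedule". Patients are not on this list.
- Concealment: "Group assignment will be concealed from patients, anesthesiologists responsible for operation, and investigators who are in charge of assessing and collecting data".
- Timing: "Group allocation will not be disclosed until all data collection is completed". The one stated exception is a concern about local anesthetic toxicity, after consultation with the principal investigator.

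Section 2.3.1 adds a masking measure. In the block group, "the anesthesiologist will cover the dressing at the relevant areas to hide the allocation". For controls, "Only the dressing will be covered in the same site of the control group without injecting normal saline". Section 2.4 places the blocks after induction of general anesthesia.

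The primary outcome is the QoR-15 at 24 h (section 2.1.1). The Introduction describes this instrument as an "outcome questionnaire reported by patients that assesses the quality of recovery following surgery and anesthesia". On protection against bias, the Discussion says that "researchers masked to the group allocation will evaluate the primary outcome" and names only the attending anesthesiologist as unmasked.

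**The concern.** Site staff cannot tell a participant which arm applies and also keep that arm from the participant until the 1-month visit. One of the instructions has to give way, and the paragraph does not say which.

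This matters because of who supplies the data. The patient answers the QoR-15 and rates pain on the NRS. A masked investigator who records the answers does not mask the person giving them, so the safeguard named in the Discussion does not cover this route. The exposure applies to the QoR-15 at 24 h, 72 h and 1 month and to the NRS at each time point. It also reaches rescue analgesia, a secondary outcome, because section 2.3.3 ties rescue to the patient's NRS score.

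There is a reporting consequence too. If the disclosure sentence was followed, a final report that repeats the concealment sentence would claim patient blinding that did not exist.

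**Working it through.** **1. The statements side by side.**

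| Statement in section 2.4 | Does the patient know the arm before the outcomes are collected? |
|---|---|
| Coordinator informs participants | Yes, if read literally |
| List of those who know the schedule | Patients not listed |
| Concealed from patients | No |
| No disclosure until data collection ends | No |

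The first row is incompatible with the third and fourth.

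**2. Which reading does the text favour?** For the literal reading:
- The next sentence opens with an inference (Therefore) and includes the coordinator among those who know the schedule. Explaining an even chance of either arm requires no knowledge of the schedule.
- Trial information and consent are already covered in section 2.2.1, before randomization.

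For a loosely worded consent statement:
- the third and fourth rows of the table;
- the absence of patients from the list of those who know;
- the dressings in both arms.

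The text does not settle the matter.

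**3. Size if patients do know their arm (illustration only).** The plan states no figure for reporting bias, so there is none to reproduce, and the shift b is an assumption.

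Inputs: SD 10.1 (section 2.1.4); n = 35 evaluable per arm, or 44 per arm (88/2); two-sided alpha 0.05; Student's t-test (section 2.5.4); true effect zero; b = 1, 2 or 4 points.

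Formulas: SE = SD × √(2/n); noncentrality = b/SE; df = 2n − 2. The rejection rate is the probability that a noncentral t variable falls beyond ± the 0.975 quantile of t on df.

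- n = 35: SE = 10.1 × √(2/35) = 2.41; df = 68; critical value 1.995.
- n = 44: SE = 10.1 × √(2/44) = 2.15; df = 86; critical value 1.988.

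| Assumed shift b | b/SE, n = 35 | Rejection rate | b/SE, n = 44 | Rejection rate |
|---|---|---|---|---|
| 0 | 0 | 5.0% | 0 | 5.0% |
| 1 | 0.41 | 6.9% | 0.46 | 7.4% |
| 2 | 0.83 | 12.9% | 0.93 | 15.1% |
| 4 | 1.66 | 37.2% | 1.86 | 45.1% |

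Almost all of the excess lies in the direction of the shift. At b = 2, the rate favouring the shifted arm alone is 12.6% (n = 35) or 14.9% (n = 44). For scale, 2 and 4 points are a quarter and a half of the 8-point difference that section 2.1.4 treats as clinically significant.

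**The case against.** The strongest reply is that most of the document intends patient blinding. Patients are listed as concealed, disclosure is deferred to the end of data collection, unblinding is reserved for a toxicity concern, patients are absent from the list of those who know, and dressings go on both arms. On this view the disclosure sentence is a clumsy way of saying that patients will be told they may or may not receive blocks. That is plausible. It stands against any claim that patients will in fact be unblinded, but it does not remove the contradiction, because the words as printed instruct disclosure and the next sentence supports that reading.

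A reader might infer that the sponsor chose an open-label design for patients, or that the primary result is bound to be biased. The documents support neither. Nothing shows that unblinding was intended, and knowledge of the arm exposes a self-reported score to bias without proving that bias occurs or how large it is.

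Two further points stand. Controls receive a dressing and no injection, so the masking is not a full sham, and it cannot be said that this one sentence alone decides whether patients remain blind. The rejection rates depend on assumed shifts and on disclosure taking place. A 1-point shift adds only about 2 percentage points, so the table does not establish how serious the problem is.

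**Conclusion.** Section 2.4 is wrong as written: it contradicts itself on whether patients know their allocation. This rests on the text alone and needs no calculation. It should be corrected because the primary outcome and the pain scores come from the patient, so assessor masking gives no protection if the disclosure sentence is followed.

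The consequence is conditional. If patients are told their arm, and if this shifts the between-arm QoR-15 difference by 1 to 4 points, the false-positive rate with no true effect rises from 5% to between about 7% and 37% (35 per arm) or 7% and 45% (44 per arm). If only the possibility of either arm was explained at consent, none of this inflation arises from the sentence, and the fault is one of wording.

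**What to change.** 1. Replace the disclosure sentence with: 'Participants will be told that they will be randomised to receive or not receive the nerve blocks, and will not be told their allocation until their 1-month assessment has been recorded, except under the unblinding provision already stated for suspected local anesthetic toxicity.'

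2. Reword the sentence that follows, which now draws its conclusion from the disclosure sentence. It should state who holds the allocation and why, consistently with the new text. Align the consent script.

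3. Section 2.1.4 says that the trial started in April 2022, so establish and report what participants already enrolled were actually told.

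4. If they were told their arm, drop the claim of patient blinding and state the limitation. Keep all randomized patients in the primary analysis, in line with the intention-to-treat population in section 2.5.4. Treat any comparison by disclosure status as exploratory. Excluding informed participants is not a remedy: if all were told, nobody remains, and if only some were, it removes patients after randomization because they knew their arm.

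The cost is two sentences in the protocol, a matching consent script and a check of what was said to those already enrolled. No extra patients or procedures are needed.
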